**ABSTRACT**

Cross Training is a high-intensity exercise modality, in which the most demanding part of training and competition is called the WOD (workout of the day). Competitions consist of multiple WODs performed in sequence and across consecutive days, which may lead to muscle fatigue and increase athletes’ susceptibility to injuries. In some sports, therapeutic devices have been used to accelerate muscle recovery or modulate the damage caused by strenuous exercise, such as photobiomodulation therapy combined with a static magnetic field (PBMT-sMF), extracorporeal shock wave therapy (ESWT), and intermittent pneumatic compression (IPC). However, it is still unclear which modality is most effective in promoting faster and more efficient muscle recovery in Cross Training athletes. Therefore, the aim of this study is to compare the isolated and combined effects of three different therapeutic modalities—PBMT-sMF, ESWT, and IPC—on muscle recovery in Cross Training athletes, as well as to investigate whether there will be adverse effects related to physiological recovery. To this end, a randomized, controlled, crossover, blinded clinical trial will be conducted. Male Cross Training athletes aged 18 to 36 years will voluntarily participate and will be randomly allocated to receive, in crossover order, the four interventions (control/passive recovery, PBMT-sMF, ESWT, and IPC) across four weeks of procedures. Muscle recovery will be assessed at baseline (prior to any intervention) and at 1 h, 24 h, and 48 h following a WOD designed to induce fatigue. Assessments will include the primary outcome: performance in a functional test; and secondary outcomes: subjective perception of effort/fatigue measured by the CR-100 scale, physiological variables through analysis of muscle damage via lactate dehydrogenase (LDH) levels, as well as thiobarbituric acid reactive substances (TBARS), carbonylated proteins, catalase (CAT), and superoxide dismutase (SOD) activity to assess oxidative stress. Data will be analyzed both in absolute values and as percentage changes from baseline (pre-exercise) values. The Kolmogorov-Smirnov test will be used to verify data normality. Statistical significance will be set at p < 0.05.

**Keywords:** Photobiomodulation Therapy, Shock Wave Therapy, Intermittent Pneumatic Compression, Fatigue, Performance, Recovery.

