**Outcomes**

The primary outcome will be the change in performance on the functional test, assessed 1-hour post-WOD. Secondary outcomes will include: change in functional test performance at 24 and 48 hours post-WOD; biochemical markers of muscle damage and oxidative stress; antioxidant activity; subjective perception of exertion (assessed at 1, 24, and 48 hours post-WOD); and satisfaction with the intervention (assessed at 48 hours post-WOD).

- Vertical Jump Performance: Vertical jump performance will be measured using the countermovement jump (CMJ) height test (Balsalobre-Fernández et al., 2015). During the test, participants will stand with feet shoulder-width apart and hands on the hips. They will perform a controlled squat to ~90° of knee flexion followed by an explosive vertical jump. Upon landing, they will flex the hips, knees, and ankles to absorb impact. A smartphone camera, positioned 1.5 m away, will record three maximal-effort CMJ attempts (Balsalobre-Fernández et al., 2015). Jump height will be analyzed using the JumPo 2 app (iOS), the only validated tool available at the time. The highest recorded jump will be used for analysis.
- Muscle Damage and Oxidative Stress Markers: Muscle damage will be assessed via lactate dehydrogenase (LDH) levels (De Oliveira et al., 2017). Oxidative stress and antioxidant activity will be assessed using thiobarbituric acid reactive substances (TBARS), carbonylated proteins, catalase (CAT), and superoxide dismutase (SOD) (Pinto et al., 2022). Blood samples (5 mL) will be drawn from the anterior cubital vein and stored at −80 °C for later analysis. LDH activity will be quantified by spectrophotometry using specific reagent kits (Labtest®, Minas Gerais, Brazil) as an indirect marker of muscle damage. TBARS, carbonylated proteins, CAT, and SOD will be analyzed as biomarkers of oxidative stress and antioxidant defense following previously established spectrophotometric protocols (Pinto et al., 2022). Each biochemical analysis will be conducted in triplicate, and the mean value will be used for statistical interpretation.
- Subjective Perception of Exertion: Perceived exertion will be assessed using the Rate of Perceived Exertion (RPE) scale (Fanchini et al., Weston et al., 2015). Participants will rate effort in two domains:
- RPE-MI (Muscular Intensity): perceived lower-limb fatigue.
- RPE-R (Respiratory Effort): perceived cardiorespiratory fatigue.

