**Statistical Analysis**

To the best of our knowledge, no prior study will have compared PBMT-sMF, IPC, ESWT, and passive recovery in Cross Training athletes. Therefore, sample size will be calculated based on CMJ performance data from the first session, following a previously described method (Pinto et al., 2022). This calculation will be conducted by a blinded researcher and will use percentage changes in CMJ at 1-hour post-WOD (primary outcome). An 80% statistical power (α = 0.05; ANOVA) will be considered, and the WebPower (https://webpower.psychstat.org/models/means03/effectsize.php) and Statistics Kingdom (https://www.statskingdom.com/sample_size_regression.html) tools will be used for the computation.

Statistical analyses will follow the intention-to-treat principle (Elkins, 2015). The statistician will remain blinded to allocation to minimize bias. Data normality will be assessed using the Shapiro–Wilk test. Differences between interventions will be evaluated using repeated-measures ANOVA with Bonferroni post hoc tests. Both absolute values and percentage changes from baseline will be analyzed. Results will be presented as mean ± SD (tables) and mean ± SEM (figures). Fisher’s exact test will be used to compare satisfaction proportions across interventions. Statistical significance will be set at p < 0.05.

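### The primary 1-hour jump outcome is to be analysed on two scales at p < 0.05 with neither named as decisive, and percentage change is usually the less precise choice

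*Protocol*

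**What the plan says.** The Outcomes section defines the primary endpoint without a scale: "The primary outcome will be the change in performance on the functional test, assessed 1-hour post-WOD". The Statistical Analysis section then states "Both absolute values and percentage changes from baseline will be analyzed", and the Abstract says the same: "Data will be analyzed both in absolute values and as percentage changes from baseline (pre-exercise) values". Neither place ranks the two scales.

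The only hint of a ranking is in the sample-size text, where the calculation "will use percentage changes in CMJ at 1-hour post-WOD (primary outcome").

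The test is described as follows: "Differences between interventions will be evaluated using repeated-measures ANOVA with Bonferroni post hoc tests". The threshold is general: "Statistical significance will be set at p < 0.05". The Bonferroni step covers comparisons between interventions, not the two scales, and no baseline covariate is mentioned.

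A pre-workout measurement is nevertheless taken in every session (Study Sessions and Exercise Protocol). For perceived exertion, the Outcomes section lists only post-workout times: "subjective perception of exertion (assessed at 1, 24, and 48 hours post-WOD").

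**The concern.** Two analyses of one primary question, each judged at 0.05 and with no order between them, give two chances of a positive finding. If one scale is significant and the other is not, the protocol offers no rule for deciding which counts.

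There is also a question of efficiency. Percentage change divides by a single session's baseline, so the noise in that baseline enters the outcome. Using the same baseline as a covariate lets the data set its weight. If the within-session correlation is modest, percentage change throws away precision that the pre-workout jump could supply, and it can do worse than ignoring the baseline.

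**Working it through.** **Inputs from the protocol.** Four interventions, each received by every participant. A pre-workout measurement in each session. α = 0.05 and 80% power. Repeated-measures ANOVA. The protocol gives no number of participants, effect size, standard deviation or pre/post correlation, so there is no stated figure to reproduce.

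**Assumptions (not in the protocol).** Mean jump 35 to 40 cm; between-participant SD about 5 to 6 cm; within-participant SD 2 cm between sessions; a 5% drop after the workout; 12 to 40 participants. ρ is the within-participant correlation between pre-workout and 1-hour jump. There were 20,000 simulated crossovers per setting.

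**Step 1: two chances at p < 0.05.** For two independent tests the chance of at least one false positive is 1 − (1 − 0.05)² = 0.0975. The two scales share data, so the simulated figure depends on what absolute means:

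| Reading of absolute | Each test alone | At least one p < 0.05 |
|---|---|---|
| Jump height at 1 hour | about 5% | 7.9% to 9.9% |
| Change in cm | about 5% | 5.4% to 6.3% |

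The second row is low because change in cm and percentage change are almost the same variable.

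**Step 2: precision.** Take equal within-participant variance σ² before and after the workout. Percentage change, converted to cm, behaves much like a simple change.

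- Change: variance 2σ²(1 − ρ)
- Baseline-adjusted height: variance σ²(1 − ρ²)
- Ratio: 2(1 − ρ)/(1 − ρ²) = 2/(1 + ρ)
- Change relative to unadjusted height: 2(1 − ρ), which exceeds 1 when ρ < 0.5

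| ρ | 2/(1 + ρ) | Simulated ratio, n = 20 | 2(1 − ρ) |
|---|---|---|---|
| 0.2 | 1.67 | 1.61 to 1.66 | 1.6 |
| 0.4 | 1.43 | 1.37 to 1.41 | 1.2 |
| 0.6 | 1.25 | 1.22 to 1.25 | 0.8 |
| 0.8 | 1.11 | 1.08 to 1.11 | 0.4 |

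**Step 3: what this means for power.** With 16 participants and an illustrative effect of 1.5 cm for one intervention:

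| ρ | Percentage change | Baseline-adjusted height |
|---|---|---|
| 0 | 0.29 | 0.52 |
| 0.25 | 0.37 | 0.55 |
| 0.5 | 0.54 | 0.66 |
| 0.75 | 0.85 | 0.89 |

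**Step 4: a case that goes the other way.** Suppose the 1-hour jump equals that session's pre-workout jump times a random factor (coefficients of variation 12% between and 5% within participants). The variance ratio is then about 0.94 to 0.97, a small advantage for percentage change. With equal variances, multiplicative errors and a correlation of 0.9, it is about 0.99 to 1.00.

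**The case against.** The strongest reply is that the protocol already identifies the primary scale. The Outcomes section speaks of a change, and the sample-size sentence attaches the primary-outcome label to percentage change. On that reading absolute values are a companion report and there is only one test of the primary question. This has weight: if percentage change is the sole confirmatory scale, the inflation disappears. But the label stands in a parenthesis about sample size, and the analysis paragraph and the Abstract put the two scales side by side. A separate analysis plan might settle the order, but the protocol itself commits to both. The precision question remains in either case.

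Three stronger readings should be avoided.

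- *That the false-positive rate is close to 10%.* This needs absolute to mean height at 1 hour, and the text does not say so. As change in cm, the excess is about one percentage point.
- *That percentage change can never be the more precise analysis.* Step 4 shows otherwise. The protocol gives no pre/post correlation and no error structure, so the loss cannot be fixed at one value. Percentage change is also a valid outcome that holds its 5% level when tested alone, so preferring adjustment is a matter of efficiency.
- *That percentage change in perceived exertion cannot be formed because no baseline rating exists.* The Outcomes section lists only post-workout ratings. However, the Abstract includes perceived effort among measures taken at baseline as well, and the session description places assessments on both sides of the workout. The documents disagree and do not rule a baseline rating out. A rating of zero at rest is possible on a 0–100 scale, but the protocol does not say it will occur.

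**Conclusion.** The point holds as a gap in specification with a moderate cost. The protocol commits to two unranked analyses of its primary outcome at p < 0.05. If both are tested, the chance of at least one false positive is roughly 5.5% to 10%, depending on the meaning of absolute.

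Percentage change usually loses precision against baseline-adjusted height: about 60% more variance at ρ = 0.2, falling to about 10% more at ρ = 0.8. There is no loss, or a gain of about 5%, if fatigue acts proportionally on the session's jump. All variance inputs are assumptions. The two-scale commitment and the missing order are in the text.

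**What to change.** 1. In Outcomes and Statistical Analysis, name one confirmatory analysis: CMJ height at 1 hour (cm), with that session's pre-workout height as covariate, in a model with participant, period and treatment. The protocol currently names only repeated-measures ANOVA, so the model must be written out.
2. Label percentage change as supportive. The adjusted difference can still be expressed as a percentage of mean baseline for readers.
3. Base the sample-size calculation on the same scale and model. In the first session each participant has received only one intervention, so the within-participant correlation cannot be read from those data. State an assumed range for it.
4. Analyse perceived exertion as the raw score, because a baseline of zero would make percentage change undefined. Reconcile the rating times in Outcomes with the baseline assessment in the Abstract and in the session description.

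The cost is a few sentences and a revised sample-size calculation. The pre-workout jump is already collected, so the primary analysis needs no new data.

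### The five blood markers are to be analysed on two unranked scales, one of them the inefficient percentage change, with a normality test that differs between sections and leads to no action; one baseline-adjusted log analysis should be named as lead

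*Protocol*

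**What the plan says.** The Statistical Analysis section sets one model for the comparisons: "Differences between interventions will be evaluated using repeated-measures ANOVA with Bonferroni post hoc tests". It then says "Both absolute values and percentage changes from baseline will be analyzed". The Abstract repeats the pair of scales and defines baseline: "Data will be analyzed both in absolute values and as percentage changes from baseline (pre-exercise) values". Neither section says which scale carries the conclusion. Results are to be summarised as means with SD or SEM.

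On distributional checks, the Abstract says "The Kolmogorov-Smirnov test will be used to verify data normality" and the Statistical Analysis section says "Data normality will be assessed using the Shapiro–Wilk test". No action is tied to either test.

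The markers appear under Outcomes as secondary outcomes. LDH represents muscle damage, and "TBARS, carbonylated proteins, CAT, and SOD will be analyzed as biomarkers of oxidative stress" and of antioxidant defence. They answer the second specific objective. The power statement ("An 80% statistical power (α = 0.05; ANOVA) will be considered") concerns jump height at 1 hour only. The protocol gives no sample size and no SD, CV or distribution for any marker.

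**The concern.** Two scales with no lead give two answers per marker and time point, each judged by the same rule ("Statistical significance will be set at p < 0.05"). If they disagree, nothing in the text says which one is the result. A normality test without a consequence, named differently in two places, leaves the same freedom: it can be cited afterwards in support of either scale.

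The scales are also not equally good. Percentage change divides each post-WOD value by a single pre-WOD value from the same session, so the noise of that baseline enters the outcome in full. In a small crossover this can cost much of the power for the marker comparisons. If the markers are right-skewed, it also makes the reported rise after exercise look larger than it is.

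**Working it through.** **Inputs.** From the protocol: four interventions compared within athlete, ANOVA with Bonferroni, alpha 0.05, two scales, and assessments before and after each WOD (read here as a pre-WOD value in every session). Four interventions give 6 pairs, so each pairwise test is at 0.05/6 = 0.0083. There is no stated figure for the markers to reproduce.

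**Assumed, not in the documents.** 16 athletes; one intervention lower by 1.2 within-athlete SDs; exercise multiplies the marker by 1.4; between-athlete log-SD 0.3; within-athlete log-SD s of 0.10, 0.25 or 0.50. Since CV² = exp(s²) − 1, these are CVs of about 10%, 25% and 53%. Let ρ be the correlation of pre and post errors within a session.

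**Step 1: why a change score is costly.** On the log scale, with athlete effects removed, the error variances are:
- post value alone: s²
- change from baseline: 2s²(1 − ρ)
- post value adjusted for baseline: s²(1 − ρ²)

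At ρ = 0 these are s², 2s² and s². At ρ = 0.5 they are s², s² and 0.75s². Adjustment is never worse than the change score; the ratio of change to adjusted variance is 2/(1 + ρ), which is 2 at ρ = 0 and 1.33 at ρ = 0.5.

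The non-centrality for one pair is 1.2 × √(16/(2v)), with v the variance in units of s² and a critical t of about 2.76 (44–45 degrees of freedom):
- ρ = 0, adjusted: 1.2 × √8 = 3.39, power about 0.73
- ρ = 0, change: 1.2 × √4 = 2.40, power about 0.37
- ρ = 0.5, adjusted: 1.2 × √(8/0.75) = 3.92, power about 0.87
- ρ = 0.5, change: 3.39, power about 0.73

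**Step 2: power of the planned scales by simulation** (log-normal data, ρ = 0, 4,000 runs).

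| Within-athlete log-SD | Raw post value | Percentage change | Log change | Log, baseline-adjusted |
|---|---|---|---|---|
| 0.10 | 0.64 | 0.32 | 0.36 | 0.72 |
| 0.25 | 0.59 | 0.27 | 0.38 | 0.74 |
| 0.50 | 0.44 | 0.15 | 0.37 | 0.71 |

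The gain of the adjusted log analysis over raw values is 0.72 − 0.64 = 0.08, 0.74 − 0.59 = 0.15 and 0.71 − 0.44 = 0.27. A repeat run gave about 0.08, 0.14 and 0.29; the differences are simulation error. Over log-normal and additive data together, percentage change has power of about 0.15–0.34 at ρ = 0 and 0.34–0.70 at ρ = 0.5; the adjusted log analysis has 0.71–0.74 and 0.85–0.88.

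**Step 3: additive normal data** (within-athlete SD 10% or 20% of baseline, ρ = 0). Raw 0.73, adjusted log 0.72–0.73, percentage change 0.16–0.21. The log analysis gains nothing here and costs at most about 0.01.

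**Step 4: disagreement between the two scales.** With a true effect and ρ = 0, raw and percentage-change tests disagreed on significance in 34–38% of log-normal trials and 55–59% of additive trials.

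**Step 5: size of the percentage change.** For log-normal data with ρ = 0, the mean of post/pre is inflated by exp(s²) = 1 + CV². A true 40% rise then reads as 1.4 × 1.04 − 1 = 45.6% at CV 20%, 1.4 × 1.09 − 1 = 52.6% at 30% and 1.4 × 1.25 − 1 = 75% at 50%. A real difference between interventions is stretched by the same 4%, 9% and 25%. At ρ = 0.5 the factor is its square root, for example √1.25 = 1.12 at CV 50%.

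**Step 6: false positives.** With no effect the inflation is the same under every intervention and cancels. In simulations of the overall F test (n = 12, 16 and 24), type I error was 0.035–0.053 on every scale, against 0.05.

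**Step 7: the two normality tests.** For log-normal samples with log-SD 0.25–0.5 and n = 12–20, Shapiro–Wilk rejects in about 10–52%. Kolmogorov-Smirnov with estimated mean and SD rejects in 0–1% uncorrected, but in 10–35% with the Lilliefors correction. The protocol does not say which form is meant.

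**The case against.** The strongest reply is that the documents do not show skewed markers. They give no SD, CV or distribution, and for additive data without within-session correlation the log scale offers nothing over raw values. That stands, and the gain over raw values is therefore stated as conditional.

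Three stronger readings are tempting and not supported:
- A reader might infer that the planned comparisons are biased or give too many false positives. They do not: null comparisons between interventions are unbiased on both scales and type I error is at or close to nominal. Raw comparisons are also unbiased for differences in arithmetic means. Only the within-intervention rise and the size of a real percentage-change difference are overstated, and only if the data are of log-normal type.
- A reader might blame skew for the low power of percentage change. The loss is as marked in additive, unskewed data; the noisy baseline is the main cause. Taking logs does not cure it either, as the log-change column shows. Nor is percentage change always worse than raw values: at ρ = 0.5 the log change and the post value alone have equal variance.
- A reader might say that the choice of normality test decides whether skew is noticed. That holds only for the uncorrected Kolmogorov-Smirnov test.

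It is also fair that transformation rules and residual checks often belong in an SAP, which is not shown here, so the absence of a log rule is not itself an error. But the protocol is not silent: it commits to two scales and a model, and it contradicts itself on the test. Blinding the statistician to allocation limits result-driven choice, but does not prevent picking the scale with the smaller p-value from coded data. Finally, the sentence on scales covers every outcome; this point is confined to the markers, which are secondary.

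**Conclusion.** The concern holds in a limited form. Evident from the text: two unranked scales, two different normality tests and no stated consequence. Shown by calculation under assumed values: percentage change is an inefficient choice for the markers, with power of about 0.15–0.34 (uncorrelated session errors) or 0.34–0.70 (correlation 0.5), against 0.71–0.74 and 0.85–0.88 for the baseline-adjusted log analysis. Against raw values the adjusted log analysis gains about 0.08 at a CV of 10%, 0.14 at 25% and 0.29 at about 50% if variation is proportional to level. It also gains if pre and post values correlate within a session, and is about neutral otherwise.

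These figures rest on 16 athletes, an effect of 1.2 within-athlete SDs and a baseline measured in each session, none of which the protocol fixes numerically. The primary outcome is not affected by this point. It is worth correcting because the better analysis uses data already collected and removes a choice that could otherwise be made after seeing the results.

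**What to change.** For LDH, TBARS, carbonylated proteins, CAT and SOD, state one lead analysis in the Statistical Analysis section: the log-transformed post-WOD value, adjusted for the log pre-WOD value of the same session, within the crossover model. Report geometric mean ratios between interventions with 95% CI; these read directly as per cent differences. Absolute values may remain as description. Percentage change should not carry the inference for these markers.

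In both the Abstract and the Statistical Analysis section, remove the normality pre-test, or name the same test in both. Either way, state that the analysis does not depend on its result, and check model residuals instead.

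The cost is wording in two sections, one transformation and one covariate in the code, with no new data. The one real trade-off is that the target becomes a ratio of geometric means instead of a difference in arithmetic means.

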**METHODS**

**Study Design and Ethics**

This randomized, controlled, crossover clinical trial with blinded outcome assessors will be prospectively registered at ClinicalTrials.gov. The study will be submitted to the Ethics Committee of Universidade Nove de Julho and conducted in accordance with the Declaration of Helsinki. Written informed consent will be obtained.

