**Blinding and Randomization**

Outcomes will be assessed by an independent evaluator who will be blinded to group allocation. Intervention sequences will be randomized (1:1:1:1) via www.randomization.org by a researcher not involved in other phases of the study. Each participant will complete all four interventions across weekly sessions with seven-day washout periods. Allocation will be concealed using sealed, numbered, opaque envelopes.

The intervention orders will be:

- Sequence 1: PR → PBMT-sMF → ESWT → IPC
- Sequence 2: PBMT-sMF → ESWT → IPC → PR
- Sequence 3: ESWT → IPC → PR → PBMT-sMF
- Sequence 4: IPC → PR → PBMT-sMF → ESWT

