**Study Sessions and Exercise Protocol**

The trial will comprise four sessions with seven-day washouts. Procedures will remain identical except for the randomized intervention applied. Assessments will occur before and after each WOD.

- Exercise Protocol – WOD: To minimize circadian and external influences, participants will perform the WOD at the same time in all sessions and will avoid physical activity from 24 h pre-WOD to 48 h post-WOD. The WOD will follow the Cross Training 21-15-9 scheme (three rounds, no rest), aiming for the fastest possible completion. Repetitions will be monitored by an independent assessor.

The exercises will include:

1. Assault AirBike Calories: Participants will use a standardized AirBike model, pedaling until they reach the target calorie count required for each round.
2. Hang Squat Clean: The exercise will start with the participant holding the barbell in the hang position (above the knees) with arms fully extended. From this position, the barbell will be cleaned to the shoulders while the hips descend below the knees. A repetition will be validated when full hip and knee extension is achieved with the bar resting on the shoulders.
3. Box Jump Over: Participants will perform a two-foot jump onto a 60.69-cm (24-inch) box, ensuring both feet contact the top surface before jumping down to the opposite side.

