  Volunteers will complete two identical RPE scales ranging from 0 to 100, corresponding to muscular and cardiorespiratory effort.
- Satisfaction with the Intervention: Satisfaction will be assessed 48 hours post-WOD using a 5-point Likert scale: (1) Very unsatisfied, (2) Unsatisfied, (3) Neutral, (4) Satisfied, (5) Very satisfied. For analysis, responses will be dichotomized as satisfied (“satisfied” and “very satisfied”) versus not satisfied (“neutral,” “unsatisfied,” and “very unsatisfied”).

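### Satisfaction is to be compared with Fisher's exact test, which assumes independent groups, although the same participants rate all four interventions

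*Protocol*

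**What the plan says.** The Study Design and Ethics section describes the study thus: "This randomized, controlled, crossover clinical trial with blinded outcome assessors". Blinding and Randomization states: "Each participant will complete all four interventions across weekly sessions with seven-day washout periods". Study Sessions and Exercise Protocol adds: "Procedures will remain identical except for the randomized intervention applied".

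In Outcomes, satisfaction with the intervention is the last-listed secondary outcome: "Satisfaction will be assessed 48 hours post-WOD using a 5-point Likert scale". The two top categories are then set against the other three: "For analysis, responses will be dichotomized as satisfied".

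Statistical Analysis gives two rules for comparing interventions. In general: "Differences between interventions will be evaluated using repeated-measures ANOVA with Bonferroni post hoc tests". For satisfaction, Fisher's "exact test will be used to compare satisfaction proportions across interventions". The threshold for both is the same: "Statistical significance will be set at p < 0.05". The satisfaction comparison is not limited to first-session ratings, and no matched method for binary data is named.

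**The concern.** Fisher's exact test, in its 2×2 form or extended to four columns, treats the columns as different people. Here each participant appears in every column. With n participants there are 4n ratings from n people, and the test takes them for ratings from 4n people.

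The same paragraph therefore handles participants as matched for the ANOVA outcomes and as independent for satisfaction. This is a stated choice of test that does not fit the stated design. It is not a detail left open for a statistical analysis plan.

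At stake is the meaning of the satisfaction p-value. If athletes who are generally positive rate all four interventions favourably, the test ignores that shared component and overstates the variability of the comparison. A finding of no difference in satisfaction could then be a product of the test. The within-person comparison, which is the reason for running a crossover, goes unused for this outcome.

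**Working it through.** **Inputs.** From the protocol: four interventions per participant, one satisfaction rating per intervention, a binary response, a threshold of 0.05. The protocol states no power or rate for satisfaction, so there is no figure to reproduce. It gives a rule for calculating the sample size but no number. The sample sizes, satisfaction rates and correlations below are assumptions.

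**Step 1: why pairing matters.** For two interventions with satisfied proportions p₁ and p₂ in the same n people and binary correlation r,

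Var(difference) = [p₁(1−p₁) + p₂(1−p₂) − 2r√(p₁(1−p₁)p₂(1−p₂))] / n.

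An independent-groups test in effect sets r = 0. With p₁ = p₂ = 0.70 and n = 20:

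- r = 0: 2 × 0.21 / 20 = 0.0210
- r = 0.28: 0.0210 × (1 − 0.28) = 0.0151
- r = 0.55: 0.0210 × (1 − 0.55) = 0.0095

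Positive r makes the assumed variance too large, so the test is conservative. Negative r makes it too small, so the test would be too liberal.

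**Step 2: an example without simulation.** Of 20 participants, 8 are satisfied with one intervention and 14 with another, and all 6 discordant participants lean the same way.

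- Fisher (8/20 vs 14/20, taken as separate people): p = 0.111.
- Exact McNemar (6 discordant, all one way): 2 × (1/2)⁶ = 0.031.

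The same data fall on opposite sides of 0.05.

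**Step 3: simulation across four interventions.** Four binary ratings per participant come from a latent normal variable with a shared participant component. The exact Fisher test on the 2×4 table is compared with Cochran's Q,

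Q = (k−1)(kΣCⱼ² − N²) / (kN − ΣRᵢ²), referred to χ² on k−1 = 3 df,

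where Cⱼ are intervention totals, Rᵢ participant totals and N the total satisfied.

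Power at n = 20, true rates 50/85/70/70%:

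| Latent correlation | Binary correlation at equal 70% rates | Fisher | Cochran's Q |
|---|---|---|---|
| 0.45 | about 0.28 | about 44% | about 62% |
| 0.77 | about 0.55 | about 38% | about 81% |

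With all four true rates at 70% and a binary correlation of about 0.28, the actual type I error at n = 20 is about 1.0% for Fisher and 4.2% for Cochran's Q.

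The 0.55 applies only to equal 70% rates. For the 50% vs 85% pair the largest possible binary correlation is √(0.5 × 0.15 / (0.5 × 0.85)) = 0.42, and at latent correlation 0.77 it is about 0.38.

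**Step 4: a second set of rates.** Type I error with all rates at 60%, and power at 40/70/70/70%, from 4,000 simulated trials per scenario at n = 20:

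| Latent correlation | Type I error, Fisher | Type I error, Q | Power, Fisher | Power, Q |
|---|---|---|---|---|
| 0 | 4.4% | 4.5% | 45.5% | 46.8% |
| 0.3 | 2.4% | 4.9% | 43.2% | 56.6% |
| 0.6 | 0.5% | 4.3% | 40.2% | 69.9% |
| 0.8 | 0.1% | 3.8% | 34.8% | 83.2% |

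At latent correlation 0.6, power is 18.6% (Fisher) vs 41.6% (Q) at n = 12, and 51.6% vs 79.4% at n = 24. The ordering does not depend on n in this range. At zero correlation the two tests are practically the same.

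**The case against.** Four arguments can be made for leaving the sentence alone or giving it little weight.

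**It is one secondary outcome.** This stands. The primary outcome, change in jump performance at 1 hour, has repeated-measures ANOVA, which respects the pairing, and the sample-size rule uses jump data only. A reader might infer that the trial's main comparison or its size is compromised. The protocol does not support that.

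**The expected error is on the safe side.** This stands under positive correlation: there would be too few false positives and a loss of power. A reader might infer that the test will produce spurious satisfaction differences. Nothing in the protocol points that way.

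**The direction is assumed.** This also stands. The protocol gives no correlation. If athletes rate by contrast, liking one method and marking down another, the correlation could be negative and the test could exceed its nominal level. It would therefore be wrong to say without condition that the true level is far below 5%. What does not depend on the correlation is that the test's independence assumption is not met by the design.

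**Collapsing five categories to two is a choice, not a mistake.** Correct. A reader might count the dichotomisation as a second error, but the cut-point is prespecified and the proportion satisfied is a legitimate summary. Some information is lost; no rule is broken.

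None of these makes an independent-groups test suitable for ratings from the same participants.

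**Conclusion.** The specified test does not match the design, and this should be corrected. Four ratings come from each participant, and Fisher's exact test treats them as coming from four separate groups.

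If ratings correlate positively within person, the consequence is a conservative test with less power than a matched one. At n = 20 and 50/85/70/70% satisfied, the loss is about 18 percentage points (44% vs 62%) at latent correlation 0.45 and about 43 points (38% vs 81%) at 0.77. These sizes rest on an assumed n, assumed rates and an assumed correlation. The loss vanishes at zero correlation, and the direction could reverse at negative correlation.

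The damage is confined to the satisfaction outcome. The primary jump analysis is unaffected.

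**What to change.** Replace the sentence on Fisher's test with a matched analysis of the same prespecified satisfied/not satisfied response. Either of these would do:

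- Cochran's Q across the four interventions, with exact McNemar pairwise tests adjusted for multiplicity, in participants who have all four ratings.
- A mixed-effects or GEE logistic model with participant as cluster and intervention and period as fixed effects, using all available ratings.

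The sentence should also say how incomplete sets are handled. Participants section exclusions for injury during the study can leave fewer than four ratings, while the analysis is declared intention-to-treat. Cochran's Q drops incomplete sets; the model does not.

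The cost is one or two sentences and no new data. There are small downsides. Cochran's Q is itself somewhat conservative in small samples or at high satisfaction: its simulated level was 2.6–3.9% at n = 12 with 70% satisfied, and 0.8–3.4% at n = 12 with 90% satisfied. If Bonferroni is used for all six pairs, the threshold is 0.05/6 = 0.0083. An exact McNemar test then needs at least 8 discordant participants, all in one direction (2 × (1/2)⁸ = 0.0078; with 7 it is 0.0156). An analysis of the full 5-point score may be added but is optional.
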